#### Missing data and withdrawals

Predictors of missing data will be investigated using regression models (including type of surgery, age, living arrangements and comorbidities) and any significant predictors will be considered for inclusion in the models. In addition, given the two assessment points at 17 and 52 weeks, we will carry out a sensitivity analysis using a joint modelling approach to check whether there is any difference in outcome (here the longitudinal outcome rather than the outcome at 17 weeks or 52 weeks alone) between the randomised arms adjusted for dropouts or missing values.

#### Instrumental variable regression

The impact of engagement with the intervention will be assessed using instrumental variable (IV) regression, using the number of face-to-face direct rehabilitation sessions over 52 weeks’ follow-up as a continuous measure of engagement. Additional exploratory IV regression analyses will use in turn: the total number of rehabilitation sessions (face-to-face plus telephone), total time (in minutes) spent in face-to-face direct rehabilitation sessions and total time (in minutes) spent in all rehabilitation sessions (ie, face-to-face and telephone). The suitability of using randomisation as the instrument in these IV regression models will be assessed using tests of exogeneity, redundancy and under/weak identification.

#### Mediation analyses

The hypothesised mechanism of change for the enhanced rehabilitation intervention is that participants’ primary outcome (activities of daily living) is mediated by self-efficacy, hip pain, cognitive function, fear of falling and physical function. If the enhanced rehabilitation intervention has a significant effect on primary outcome (p<0.05) for enhanced rehabilitation in ANCOVA, causal mediation analysis will be used to determine whether each of these potential mediators predict change in NEADL at 52 weeks. Initial assessments will determine whether the randomised intervention affects each putative mediator in turn. For those putative mediators that are significantly (p<0.1) affected by the randomised intervention, mediation analysis will be carried out adjusting for baseline covariates that predict both the mediator and NEADL, potentially including type of surgery, age, living arrangements (alone/with others) and comorbidities. Sensitivity analyses will assess the potential impact of unmeasured confounding between the mediator and NEADL.

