**Methods and analysis:**

Protocol for phase III, parallel-group, two-armed, superiority, pragmatic RCT with 1:1 allocation ratio; allocation sequence by minimisation programme with a built-in random element; secure web-based allocation concealment. The two treatments will be usual care (control) and usual care plus an enhanced rehabilitation programme (intervention). The enhanced rehabilitation will consist of a patient-held information workbook, goal setting diary and up to six additional therapy sessions. Outcome assessment and statistical analysis will be performed blind; patient and carer participants will be unblinded. Outcomes will be measured at baseline, 17 and 52 weeks’ follow-up. Primary outcome at 52 weeks will be the Nottingham Extended Activities of Daily Living scale. Secondary outcomes will measure anxiety and depression, health utility, cognitive status, hip pain intensity, falls self-efficacy, fear of falling, grip strength and physical function. Carer strain, anxiety and depression will be measured in carers. All safety events will be recorded, and serious adverse events will be assessed to determine whether they are related to the intervention and expected. Concurrent economic evaluation will be a cost-utility analysis from a health service and personal social care perspective. An embedded process evaluation will determine the mechanisms and processes that explain the implementation and impacts of the enhanced rehabilitation programme.

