### Secondary objectives

To compare the cost-effectiveness of an enhanced rehabilitation programme following surgical repair of proximal femoral fracture in older people compared with usual care at 52 weeks follow-up.To determine the effectiveness of an enhanced rehabilitation programme following surgical repair of proximal femoral fracture in older people compared with usual care, in terms of the performance of activities of daily living at 17 weeks follow-up.To determine the effectiveness of an enhanced rehabilitation package following surgical repair of proximal femoral fracture in older people compared with usual care, in terms of anxiety and depression at 17 and 52 weeks follow-up.To assess whether the enhanced rehabilitation intervention creates change in self-efficacy, hip pain, cognitive function, fear of falling and physical function as potential mediators for improving activities of daily living at 17 and 52 weeks follow-up.To assess whether the enhanced rehabilitation intervention creates change in strain, anxiety and depression in carers at 17 and 52 weeks follow-up.To determine the mechanisms and processes that explain the implementation and impacts of the enhanced rehabilitation programme and whether there are adverse effects.

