#### Analysis of effectiveness

Primary and secondary outcomes at baseline, 17 weeks’ and 52 weeks’ follow-up will be summarised for each treatment group using descriptive statistics at each time point. If normally distributed, the difference between group means (with 95% CIs) will be reported from the ANCOVA adjusted for baseline score and stratification factors.

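### Mediation analysis runs only if the primary p<0.05, and then only for mediators with p<0.1: a neutral trial yields no indirect-effect estimate, and mediator effects that pass the second filter are biased away from zero

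*Protocol article*

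**What the plan says.** The Mediation analyses section of the protocol article names the hypothesised mechanism: the effect on activities of daily living "is mediated by self-efficacy, hip pain, cognitive function, fear of falling and physical function". It then sets two conditions in sequence.

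- First filter, on the primary outcome: "If the enhanced rehabilitation intervention has a significant effect on primary outcome (p<0.05) for enhanced rehabilitation in ANCOVA, causal mediation analysis will be used".
- Second filter, on each mediator: "For those putative mediators that are significantly (p<0.1) affected by the randomised intervention, mediation analysis will be carried out".

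The one safeguard named there is a sensitivity analysis for unmeasured confounding between mediator and NEADL.

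The matching item under Secondary objectives carries no condition. For both follow-up times, it asks whether the programme "creates change in self-efficacy, hip pain, cognitive function, fear of falling and physical function as potential mediators for improving activities of daily living".

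Two other places bear on the point. The abstract lists the mediators among the secondary outcomes: "Secondary outcomes will measure anxiety and depression, health utility, cognitive status, hip pain intensity, falls self-efficacy, fear of falling, grip strength and physical function". Under Analysis of effectiveness, which covers primary and secondary outcomes, "the difference between group means (with 95% CIs) will be reported from the ANCOVA adjusted for baseline score and stratification factors". That reporting depends on normality but not on any p-value.

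**The concern.** A causal mediation analysis needs neither a significant total effect nor a significant effect on the mediator. A real indirect effect can coexist with a non-significant total effect when the primary test misses a true but smaller effect, or when direct and indirect paths pull in opposite directions. The first filter removes the analysis in just those cases.

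The second filter selects on the same estimate that is then carried forward. The indirect effect is built from the intervention's effect on the mediator, so keeping only mediators with p<0.1 keeps the estimates that chance has pushed away from zero. A sensitivity analysis for unmeasured confounding does not address that selection.

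At stake is one part of one secondary objective: whether movement in self-efficacy, pain, cognition, fear of falling or physical function translates into NEADL. That matters in a trial of a complex intervention with a stated mechanism, and the data are collected whatever the primary result.

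**Working it through.** **Inputs from the Sample size calculation section.** Difference 2.4 NEADL points, SD 10, covariate R² 0.52, alpha 5% (sidedness not stated; two-sided assumed), power 90%, retention 79%. Allocation is 1:1.

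**The plan's own figure.** Residual SD = 10 × √(1 − 0.52) = 6.93. Per arm, n = 2 × 48 × (1.960 + 1.282)² / 2.4² = 175.1, rounded up to 176, so 352 completers. 352 / 0.79 = 445.6, so 446 recruited. Both stated figures reproduce.

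**First filter (primary p<0.05).** SE of the adjusted difference = 6.93 × √(2/176) = 0.739. The probability of passing is Φ(δ/SE − 1.96) + Φ(−δ/SE − 1.96).

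| True effect δ | δ/SE | Passes | Mediation not run |
|---|---|---|---|
| 3.0 (feasibility estimate) | 4.06 | 98.2% | 2% |
| 2.4 (design) | 3.25 | 90.1% | 10% |
| 1.5 (assumed) | 2.03 | 52.8% | 47% |
| 1.2 (assumed, half the design effect) | 1.62 | 36.9% | 63% |
| 0 | 0 | 5% | 95% |

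In a simulated case with opposing paths (indirect effect 1.2, total effect 0), the first filter was passed in only 5% of 6,000 trials.

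**Second filter (mediator p<0.1).** The documents give no mediator effect sizes and no baseline correlations for the mediators, so both are assumptions. In SD units, with 176 per arm, SE = √(2(1 − R²)/176). This is 0.107 at R² = 0 and 0.074 at R² = 0.52. Because the planned ANCOVA adjusts for baseline score, R² is varied from 0 to the 0.52 used for NEADL. With μ = d/SE and cut-off 1.645, the expected estimate given a pass is the mean of the normal distribution restricted to |z| > 1.645.

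| True mediator effect d | R² | Fails filter | Overstatement when it passes |
|---|---|---|---|
| 0.2 SD | 0 | 41% | 35% |
| 0.2 SD | 0.25 | 30% | 23% |
| 0.2 SD | 0.52 | 14% | 10% |
| 0.3 SD | 0 | 12% | 8% |
| 0.3 SD | 0.25 | 5% | 4% |
| 0.3 SD | 0.52 | under 1% | under 1% |

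Worked line for 0.2 SD at R² = 0.52: μ = 0.2/0.0739 = 2.71; P(pass) = Φ(2.71 − 1.645) = 0.856; mean z given a pass is 1.098 × μ.

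The Short Physical Performance Battery has no baseline measurement in Table 2, so it gets no adjustment for its own baseline and lies nearer the R² = 0 end.

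**Both filters together.** This was simulated with 6,000 trials per scenario, unadjusted mediators and an assumed 3 NEADL points per mediator SD. At a total effect of 2.4 and a mediator effect of 0.2 SD (true indirect effect 0.60), the mean indirect effect is 0.600 over all trials and 0.812 over trials passing both filters, a ratio of 1.35. At 0.3 SD the ratio is 1.10; at 0.4 SD it is 1.03.

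**Does the second filter screen out noise?** If five independent mediators were all unaffected, at least one would still pass with probability 1 − 0.9⁵ = 41%.

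**The case against.** The strongest reply is that little is lost. The objective's verb is to assess whether the intervention creates change in the five constructs, and they are secondary outcomes reported by ANCOVA with 95% CIs whatever the primary p-value. A reader might infer from the two filters that the objective goes unanswered in a neutral trial. The documents do not support that: change in each mediator is still reported. A separate objective, "To determine the mechanisms and processes that explain the implementation and impacts of the enhanced rehabilitation programme", is served by the process evaluation, which has no significance condition. This part of the reply stands. It does not cover the link from mediator to NEADL: the process evaluation uses thematic analysis and descriptive statistics, and ANCOVAs read side by side do not estimate an indirect effect.

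A reader might also take the inflation of a significant total effect as a measure of the harm. At an assumed true effect of 1.5, significant results average 2.06, which is 37% too high. That would describe any significant result and is not an indirect-effect figure; the primary difference is reported whatever its p-value. It falls to 6% at 2.4 and 1% at 3.0.

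Two further readings do not hold as errors. The covariate list might seem to leave out baseline NEADL and the baseline mediator, but the list is open, and both would meet its criterion of predicting mediator and outcome. The mediator's time point is not tied to 17 weeks, but that is detail commonly left to the statistical analysis plan, which is not shown.

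Finally, the filters are prespecified and limit the number of exploratory tests. That is true, but labelling the estimates explanatory and giving intervals achieves the same restraint without selecting on p-values.

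**Conclusion.** The point holds in a limited form. Followed as written, the protocol gives no quantitative estimate of mediation in a neutral trial, and no unfiltered mediation estimate is planned anywhere in the article. On the protocol's own inputs this happens in 10% of trials at the design effect and in 47% if the true effect were 1.5, a value assumed here. The p<0.1 filter biases surviving mediator effects away from zero. The bias is material at about 0.2 SD (35% down to 10%, depending on baseline R²) and small at 0.3 SD (8% to under 1%). These sizes rest on a two-sided 5% test, 176 completers per arm for every measure, and assumed mediator effects and baseline correlations. The defect is confined to a secondary explanatory analysis. It is worth correcting because the rule is explicit and the remedy is cheap.

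**What to change.** Delete both significance conditions from the Mediation analyses section. State that direct and indirect effects on 52-week NEADL will be estimated with 95% CIs for all five prespecified mediators whatever the primary and mediator p-values, and labelled explanatory. Keep the planned sensitivity analysis for unmeasured confounding.

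As an optional clarification, not the correction of an error, name the 17-week measurement as the mediator, and name adjustment for baseline NEADL and for the baseline mediator where one was measured.

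The cost is a change of wording and a few more exploratory estimates to report and interpret with caution. No new data are needed, and the primary analysis and sample size do not change.

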### Economic analysis

The enhanced rehabilitation programme will be fully costed using unit costs from a public sector multiagency perspective. Unit costs will be obtained from national sources of reference costs^43 44^ and applied to information received from pilot questionnaires, namely, salary band of therapists, time spent with the patient conducting rehabilitation, costs of travel and costs of any additional equipment. Costs of health and social care services used by the participants will also be costed using national sources of reference costs. The costs of service use and the cost of the intervention will be added together for use in a cost-effectiveness analysis.

The EQ-5D (3L) will be used to calculate Quality Adjusted Life Years (QALYs) over the 52-week trial period, using the area under the curve method.^45 46^ A cost-utility analysis will be conducted to calculate a cost per QALY of the enhanced rehabilitation intervention. This cost per QALY generated will be compared with the NICE threshold range of £30 000 per QALY.^47^ We will bootstrap differences in costs and outcomes (EQ-5D-3L) between the two groups, producing a 95% CI around these differences.

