## Methods and analysis

### Trial design

This is a pragmatic, multisite, parallel-group, two-armed, superiority RCT with 1:1 allocation ratio and an internal pilot phase (figure 1). Outcome assessment and statistical analysis will be blinded; patient and carer participants and clinicians will be unblinded. A concurrent economic evaluation will be a cost-utility analysis from a health service and personal social care perspective. An embedded process evaluation will examine the mechanisms and processes that explain the implementation and impacts of the enhanced rehabilitation programme. The RCT was registered on 23 November 2018. Trial registration data can be found in online supplemental appendix 1.

10.1136/bmjopen-2020-039791.supp1Supplementary data

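### The economic analysis names no baseline-utility adjustment for the bootstrapped differences, although baseline EQ-5D-3L is part of every QALY; separately, the costing perspective and the threshold are worded inconsistently

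*Protocol article*

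**What the plan says.** The protocol article's Economic analysis section will "calculate Quality Adjusted Life Years (QALYs) over the 52-week trial period, using the area under the curve method". The Abstract fixes the time points: "Outcomes will be measured at baseline, 17 and 52 weeks’ follow-up"; Table 2 shows EQ-5D-3L at all three. The only between-group method in the economic section is "We will bootstrap differences in costs and outcomes (EQ-5D-3L) between the two groups, producing a 95% CI around these differences". It mentions no covariate. By contrast, the Analysis of effectiveness section adjusts the ANCOVA for the baseline score and the stratification factors.

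On perspective, Trial design states: "A concurrent economic evaluation will be a cost-utility analysis from a health service and personal social care perspective". The Abstract and the strengths and limitations box agree. The Economic analysis section, however, says the programme is to be "fully costed using unit costs from a public sector multiagency perspective", and then adds that cost to the cost of health and social care use to form one total. The resulting cost per QALY is to be "compared with the NICE threshold range of" £30 000 per QALY, which is a single value.

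**The concern.** An area-under-the-curve QALY starts from the baseline utility. If the arms differ at baseline by chance, an unadjusted QALY difference includes part of that difference by construction. It includes more if baseline predicts the follow-up values. Adjusting for baseline removes this and usually narrows the interval. The article writes such adjustment in for effectiveness but not for the economic comparison, so as it stands the text permits a raw comparison where an adjusted one is plainly better. Cost-effectiveness is the first-listed secondary objective, and the result is to be judged against a threshold, so a shift of a few hundredths of a QALY could matter.

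Two further points concern definition. Two perspective labels feed one cost total, so it is not fixed which costs may count. A threshold called a range but given as one number leaves the decision rule unclear.

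**Working it through.** **Inputs from the document.** EQ-5D-3L at 0, 17 and 52 weeks; 1:1 allocation; 352 completers (Sample size calculation). The 352 reproduces: with residual SD 10 × √(1 − 0.52), difference 2.4, two-sided 5% and 90% power, the requirement is 176 per arm, or 352. Then 352/0.79 = 445.6, rounded up to 446. Neither figure is in dispute. The document states no precision for QALYs or costs.

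**Assumptions, none of them in the document.** Utility SD 0.30 at each visit; correlation 0.6 between weeks 17 and 52; the same correlation ρ between baseline and each follow-up, varied from 0 to 0.5; all 352 completers contribute QALYs.

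**Step 1: weights.** With straight lines between visits over 52 weeks:
- baseline: 17/(2 × 52) = 17/104 = 0.163
- week 17: (17 + 35)/104 = 0.500
- week 52: 35/104 = 0.337

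**Step 2: chance imbalance.** SE of the baseline difference = 0.30 × √(4/352) = 0.032, so 2 SE = 0.064. The mechanical effect on the QALY difference is 0.163 × 0.064 = 0.010.

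**Step 3: total shift.** Slope of QALY on baseline = 0.163 + ρ × (0.500 + 0.337).
- ρ = 0.3: slope 0.414; shift 0.414 × 0.064 = about 0.027
- ρ = 0.5: slope 0.582; shift 0.582 × 0.064 = about 0.037

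At £30 000 per QALY, 0.010 is worth about £300 per patient, and 0.027 to 0.037 about £800 to £1100.

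**Step 4: precision.** Let r be the correlation of the QALY with baseline utility: r = slope/√(w′Rw), where w holds the weights and R the correlations. Adjusted SE / unadjusted SE = √(1 − r²).

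| ρ | r | Unadjusted SE | Adjusted SE | Reduction |
|---|---|---|---|---|
| 0 | 0.212 | 0.0246 | 0.0240 | 2% |
| 0.2 | 0.411 | 0.0257 | 0.0234 | 9% |
| 0.3 | 0.505 | 0.0263 | 0.0227 | 14% |
| 0.5 | 0.681 | 0.0273 | 0.0200 | 27% |

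The percentages do not depend on the SD or the sample size, provided the SD is common to the visits. They do depend on the follow-up correlation: with every correlation at 0.3, r² is 0.30 rather than 0.25.

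**Step 5: perspective and threshold.** No arithmetic applies. Three places name health service and personal social care. The Economic analysis section names a public sector multiagency perspective for the programme cost and pools that cost with health and social care use. The threshold sentence speaks of a range and supplies one figure.

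**The case against.** The strongest objection is that a reader might infer that the comparison will be unadjusted, and the article does not say so. A bootstrap is a resampling method, and the resampled statistic may be a regression-adjusted difference. Covariates are often left to a full protocol or a health economics plan, and neither is shown. This stands: non-adjustment is not established, only left open. What remains is the contrast within one article, where adjustment is written for effectiveness and not for the economic comparison.

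A reader might also infer bias. Under randomisation a raw difference is unbiased on average; the loss is precision, plus the effect of whatever imbalance actually occurs. The size is assumption-driven, a 2-SE imbalance is roughly a 1-in-20 event, and if early postoperative utility predicts later utility poorly the gain is small.

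The parenthesis naming EQ-5D-3L might suggest that utilities rather than QALYs are bootstrapped. The same paragraph has already converted EQ-5D-3L to QALYs, so it may simply name the instrument. Likewise, intervals around the two differences do not rule out paired resampling.

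Finally, the perspective conflict is narrow. The programme items listed are therapist salary band, time, travel and equipment, and service use is health and social care only. No cost from another agency is named, and no numerical effect is shown. It would be wrong to infer that the two labels make the cost per QALY noisier or open to imbalance; they bear only on which costs count.

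**Conclusion.** The point holds as a request to fix the wording, not as a demonstrated flaw in the analysis. Baseline utility makes up 16% of the QALY weighting, and the article names no adjustment for it. Under the stated assumptions, adjustment would reduce the SE of the QALY difference by between 2% and 27%. It would also remove a shift that, at a 2-SE imbalance, ranges from 0.010 QALY with no baseline-to-follow-up correlation to about 0.037 at correlation 0.5. The weights are certain; the SD and correlations are not in the document. The perspective mismatch and the one-value range are on the page and need reconciling, but they are separate matters of definition. The primary NEADL analysis is unaffected.

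**What to change.** In the economic plan:

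- Within each bootstrap replicate, resample patients' cost-QALY pairs and estimate the QALY difference by regression on arm, baseline EQ-5D-3L and the minimisation factors. Say explicitly that the outcome is the QALY.
- Adjust the cost difference for baseline Client Service Receipt Inventory cost only as far as the reduced baseline version (Outcomes section) allows.
- Report joint uncertainty as the probability of cost-effectiveness at the stated £30 000 per QALY.
- Name one base-case perspective and use it in the Abstract, Trial design and Economic analysis. If another perspective is kept as a sensitivity analysis, say where its data come from: Table 1 describes the inventory as covering health and social care services only.
- Give the threshold as a single value, or state both ends of a true range.

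The cost is wording. Baseline EQ-5D-3L and the reduced baseline inventory are already scheduled, so no new data collection is needed for the adjusted base case.
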